## Assignment of interventions: allocation

### Sequence generation {16a}

After baseline assessments, the participants are randomly allocated by the ALEA randomization software (ALEA Clinical Services B.V, 2023, The Netherlands) to either BFR-T or UC at a 1:1 ratio using a blocked computer-generated sequence.

### Concealment mechanism {16b}

Allocation concealment will be ensured as the ALEA randomization software will not release the randomization code until the patient has been recruited into the trial.

### Implementation {16c}

Immediately following baseline testing the research study team will enter information in the ALEA randomization software and inform the participant of the assigned intervention group.

## Assignment of interventions: blinding

### Who will be blinded {17a}

As this is an exercise intervention, participants, local study nurses, or investigators cannot be blinded to group assignment. Outcome assessors are not blinded to group allocation, except for assessors of muscle biopsy and blood samples who are blinded to group allocation. The health care providers and surgeons are not blinded to group allocation since they may discuss the intervention with the patients.

### Procedure for unblinding if needed {17b}

As this is an exercise intervention, participants cannot be blinded to group assignment and a participant’s allocated intervention will be revealed to the participant immediately following baseline testing.

## Data collection and management

### Plans for assessment and collection of outcomes {18a}

#### Study instruments

Skeletal muscle thickness and skeletal muscle cross-sectional area will be determined by ultrasound. Ultrasound serves as an imaging method capable of assessing the thickness and cross-sectional areas of surface-level muscles, such as the rectus femoris muscle. Its portability is a notable advantage. Numerous studies have validated the reliability of ultrasound in measuring the quadriceps muscle size in healthy individuals and patients in other settings [15].

Self-reported fatigue will be assessed by means of the validated EORTC Fatigue questionnaire EORTC QLQ-FA12 [16, 17]. The EORTC QLQ-FA12 is a multidimensional instrument that measures various aspects of cancer-related fatigue, including overall, physical, emotional, and cognitive aspects. Fatigue scores obtained from the questionnaire are transformed into scales ranging from 0 to 100. Higher scores on the scales indicate a higher level of cancer-related fatigue. Missing data will be handled according to the guidelines provided in the EORTC scoring manual.HRQoL will be assessed by means of the validated EORTC-QLQ-C30 [15]. The EORTC QLQ-C30 is a 30-item questionnaire that assesses the quality of life in cancer patients with five multi-item functional scales (physical, role, cognitive, emotional, and social); one global quality of life scale; three symptom scales (fatigue, pain, and nausea/vomiting) and six single-items measuring symptoms common among patients with cancer in general (dyspnea, insomnia, appetite, constipation, and diarrhea) and financial impact. The HRQoL scores will be transformed into a scale ranging from 0 to 100 where higher scores for function and/or global QOL correspond to better HRQoL, while higher scores for symptoms represent worse problems. Missing data will be handled according to the guidelines provided in the EORTC scoring manual.Nutritional status will be assessed by means of the PG-SGA scale [18]. The PG-SGA has four components, nutritional status, the physical examination, disease/condition and metabolic demand assessment components, and medical history component (comprising weight history, food intake, nutrition impact symptoms, as well as activities and function component). All four components are self-reported by patients. A total score is calculated by summing the scores from the four components, where higher scores indicate worse nutritional status.Physical function will be assessed by the short physical performance battery that includes the side-by-side stand (10 s), the semi-tandem stand (10 s), tandem stand (s), gait speed test (s), and chair stand test — 5 times (s). A total score will be calculated for the battery of tests included in short physical performance. Muscle strength is being assessed by a hydraulic hand dynamometer (JAMAR, SAEHAN corporation, Chang-won, S. Korea), and isometric muscle strength tests measuring upper and lower limb muscle strength by leg extension and chest press using a power meter (Swedish site: HUR, Ab HUR Oy, Kokkolac, Finland. Norwegian site: Gym2000, Vikersund, Norway; Strain gauge: U2A 200, Hottinger Baldwin Mestechnik, Darmstadt, Germanuý (custom made amplifier); data acquisition: Labview, National Instruments, TX, USA (custom built)). Cardiovascular fitness is assessed, both predicted and maximal oxygen uptake (VO_2peak_), through the validated sub-maximal Ekblom-Bak test [19] and a ramp test on a cycle ergometer to exhaustion which has been shown to accurately predict VO_2peak_ [20], (LODE, Lode BV, Groningen, The Netherlands).

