### Trial design {8}

This Prev-Ex is a multi-center, two-armed randomized controlled trial (RCT) with 1:1 allocation ratio, stratified for research site, and testing the superiority of the intervention. Patients diagnosed with resectable pancreatic, biliary tract, and liver cancer are randomized to an exercise program consisting of home-based low-load BFR-T during both a pre- and postoperative period consisting of a total of 6–10 weeks, or a control group. Besides the nutritional support offered as standard care for these patients, protein supplementation will be given to both groups to ensure adequate protein intake. See Fig. 1 for the modified SPIRIT study flow chart.

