### Secondary outcomes

➢ Skeletal muscle molecular characteristics will be assessed in skeletal muscle vastus lateralis biopsy tissues from participants included in the study who agree to undergo the biopsy procedure (only at the Norwegian site: T0, T3).
◦ Myogenic stem cell count◦ Autophagy◦ Capillary number per muscle fiber◦ Macrophage infiltration◦ Markers of skeletal muscle catabolism➢ Patient-reported outcome measures (T0, T1, T2, T3, T4)◦ Self-reported fatigue assessed by means of the validated European Organization for Research and Treatment of Cancer Fatigue questionnaire (EORTC QLQ-FA12).◦ Health-related quality of life (HRQoL) assessed by means of the validated Quality of Life Core Questionnaire (EORTC-QLQ-C30)◦ Nutritional status will be assessed by means of the validated Patient-Generated Subjective Global Assessment scale (PG-SGA).➢ Physical fitness/performance/activity
◦ Physical function determined by the short physical performance battery and a submaximal and maximal (ramp) cycle test to evaluate cardiorespiratory fitness and maximal isometric muscle strength evaluated in a standardized manner (T0, T1, T2, T3)◦ Objectively measured physical activity and sedentary behavior using the Fitbit activity monitor (T0, T1, T2, T3, T4)➢ Clinical outcomes will be recorded retrospectively from the patient’s medical records (T4)
◦ Hospitalization rates◦ Blood status➢ Vital signs and anthropometrics
◦ Body composition using bioimpedance analysis (T0, T1, T2, T3)◦ Body composition using dual x-ray absorptiometry (only at the Norwegian site: T0, T3)◦ Body composition will also be measured using computed tomography (CT) scans when performed as a routine measurement for the patients (T0, T4). Thus, no extra CT scans will be conducted for the purpose of this study to minimize exposure to radiation.➢ Explorative outcomes

Patient’s experience of the exercise program, protein supplement, and activity tracker through focus group or individual interviews will take place sometime following the exercise intervention for a voluntary subset of the included participants in the exercise group.

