## Statistical methods

### Statistical methods for primary and secondary outcomes {20a}

Data will be analyzed using the IBM SPSS (Statistical Package for the Social Sciences) 26 statistical package for Windows (SPSS, Chicago, IL, USA). For the quantitative analysis, descriptive statistics, ANOVA, and chi-squared tests will be used to describe and compare baseline characteristics. For longitudinal analysis, linear mixed modeling adjusted for baseline values (T0) of the outcome will be used to detect any significant differences between the two groups from pre- to post-intervention as well as at follow-up 6 months following surgery. Group-by-time interaction will be included as a fixed effect. Corresponding effect sizes will also be calculated. Chi-squared tests and corresponding odds ratios will be calculated for hospitalization rates. All tests will be 2-tailed and statistical significance set at *p* ≤ 0.05.

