### Methods for additional analyses (e.g., subgroup analyses) {20b}

For the primary outcome the model will, besides being adjusted for the baseline value, also be adjusted for diagnosis and type of surgery. Per protocol analysis for those who have adhered to the exercise program will be performed. Potential moderators of the exercise effect will be explored (e.g., age, sex, type of surgery, diagnosis). In addition, mediation analyses will be performed to explore potential underlying mechanisms of exercise effects (e.g., blood and muscle biomarkers). A subgroup analysis will also be performed to assess the rehabilitation effect only considering that some patients have a very limited time to exercise prior to surgery or may not be included until T2 due to very short time-to-surgery.

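### Leg-extension and chest-press strength is measured with different equipment at the two sites, comparability of the readings is not shown, and the stated model has no site term

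*Protocol article*

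**What the plan says.** The Secondary outcomes section lists "maximal isometric muscle strength evaluated in a standardized manner (T0, T1, T2, T3"), with no unit. Under Study instruments ({18a}), the strength tests beyond handgrip are described as "isometric muscle strength tests measuring upper and lower limb muscle strength by leg extension and chest press using a power meter", and the equipment is then given separately by site: "Swedish site: HUR, Ab HUR Oy, Kokkolac, Finland. Norwegian site: Gym2000, Vikersund, Norway; Strain gauge: U2A 200". The Norwegian chain also has a custom-made amplifier and "data acquisition: Labview, National Instruments, TX, USA (custom built"). One hand dynamometer is named for grip, with no split by site.

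Trial design {8} sets randomization "with 1:1 allocation ratio, stratified for research site". Section {20a} says "linear mixed modeling adjusted for baseline values (T0) of the outcome will be used to detect any significant differences between the two groups", with a group-by-time interaction, and adds: "Corresponding effect sizes will also be calculated". Section {20b} extends the adjustment: "For the primary outcome the model will, besides being adjusted for the baseline value, also be adjusted for diagnosis and type of surgery". Site is in neither list. The Participant timeline {13} and the Discussion allow entry at T2 when surgery comes too soon for a T0 visit. The Discussion gives the shorter wait for surgery at the Norwegian site as the reason.

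**The concern.** Two machines that differ in geometry, set-up or calibration can give different readings for the same patient, by a constant offset, by a scale factor, or both. The article describes no cross-calibration, so neither can be ruled out.

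An offset is mostly removed by adjusting for the patient's own T0 reading, but only where there is one. A scale factor also stretches the treatment effect and the residual spread at one site. One pooled, unscaled difference is then a weighted average of two differently scaled effects, and its size depends on how many patients each site contributes. Strength is a named secondary aim and a stated hypothesis, so readers will want to interpret the size of this effect and not only its p-value.

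**Working it through.** **Plan's own figure.** The protocol gives no power or sample-size figure for strength. Its 42 evaluable participants are derived for muscle thickness. The figure reproduces if the 0.8 mm standard error of measurement is multiplied by √2: n per arm = 2 × (1.96 + 0.84)² × (0.8√2)² / 1² = 2 × 7.85 × 1.28 = 20.1, so 21 per arm. It is used below only to set the trial size.

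**Size of the pooled difference.** Let d be the true effect in Swedish-device units, r the factor by which Norwegian readings are scaled, and p the Norwegian share of patients. The unscaled pooled difference is about d × [1 + p(r − 1)]. With p = 1/2 (an assumption; the protocol gives no split by site) this is d(1 + r)/2. Taking d = 10.4, the simulated raw difference on identical devices for a true 10% gain with mean strength near 100:

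| r | 10.4 × (1 + r)/2 | simulated |
|---|---|---|
| 1 | 10.4 | 10.4 |
| 1.25 | 11.7 | 11.7 |
| 1.5 | 13.0 | 13.1 |
| 2 | 15.6 | 15.5 |
| 3 | 20.8 | 20.8 |

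A site intercept does not change this: with site in the raw-scale model the simulated difference was still 15.5 at r = 2 and 20.6 at r = 3.

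**Power, multiplicative differences only.** Assumed: 20 patients per site, a 10% gain, log-SDs of 0.30 between patients, 0.07 for baseline error and 0.12 for follow-up error; 20,000 simulated trials with common random numbers. A single-follow-up ANCOVA stands in for the mixed model.

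| r | raw scale | loss against r = 1 | log scale with site |
|---|---|---|---|
| 1 | 0.520 | – | 0.554 |
| 1.25 | 0.517 | 0.003 | 0.554 |
| 1.5 | 0.510 | 0.010 | 0.554 |
| 2 | 0.488 | 0.032 | 0.554 |
| 3 | 0.446 | 0.074 | 0.554 |

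The log column is constant because log(rY) = log r + log Y and log(rB) = log r + log B. With baseline slope β the shift is (1 − β) log r, which the site term absorbs exactly. The gap at r = 1, 0.554 − 0.520 = 0.034, has nothing to do with devices; it arises because the simulated data are log-normal.

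**Power, scale and offset together.** Assumed: 21 per arm, sites about even and balanced across arms, baseline–follow-up correlation 0.8, effect 0.5 SD, mean 4 SD; simulation error about ±1.6 points.

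| Norwegian readings | raw, T0 only | raw plus site | standardized within site |
|---|---|---|---|
| same as Swedish | 0.74 | 0.74 | 0.73 |
| offset 2 SD | 0.72 | 0.73 | 0.73 |
| ×1.1 | 0.74 | 0.74 | 0.74 |
| ×1.25, offset 1 SD | 0.71 | 0.73 | 0.73 |
| ×1.5, offset 1 SD | 0.68 | 0.72 | 0.72 |
| ×2, offset 1 SD | 0.64 | 0.69 | 0.72 |

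Type I error of the raw model was 4.4 to 5.1% in every null case. The raw estimate again moved with scale, from 0.50 to about 0.56 at 1.25-fold and 0.73 at twofold, while the within-site standardized estimate stayed near 0.52.

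**Patients without T0.** With a within-site baseline slope of 0.8, adjustment leaves at most (1 − 0.8) = 0.2 of an offset, so at most 0.4 SD of a 2 SD offset. A patient kept in the model with no baseline of their own carries the full 2 SD unless site is in the model.

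**The case against.** The strongest reply is that little is shown to be wrong. Different manufacturers do not mean different units, and both devices may report the same physical quantity. A reader might infer that the pooled result has no common unit, or that raw units will be analysed. The documents support neither: no unit, scale or transformation is stated for strength, and effect sizes are promised without a metric. A reader might also see a contradiction with the claim of standardized evaluation, but that phrase can describe the test procedure and does not promise identical hardware. Nor is the whole Norwegian device custom-built; only its amplifier and data acquisition are so described. All of this stands.

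It also stands that stratification by site protects the comparison, and that a marked loss of precision cannot be claimed. Most of the log scale's advantage in power at moderate device ratios is present with identical devices, and no ratio between the devices appears in the document. A site term is not useless either: where scale and offset both differ, it recovers part or all of the lost power.

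Finally, scaling of a secondary outcome may be settled in a fuller analysis plan. That limits the weight of the point but does not remove it: the article names the stratification factor and lists the adjustment variables, and the two do not match.

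**Conclusion.** The point holds in a limited form and is minor. The equipment differs by site, comparability is not shown, and the stratification factor is missing from the stated model. The test of BFR-T against control remains valid. The loss of power attributable to devices is about 1 point or less up to a 1.5-fold pure scale difference. With an offset as well, it is about 3 points at 1.25-fold, 6 at 1.5-fold (0.74 − 0.68) and 10 at twofold (0.74 − 0.64).

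The firmer consequence is for interpretation: an unscaled pooled difference would vary with the device mix, by 25% at r = 1.5 and 50% at r = 2 when the sites are equal in size. These sizes rest on assumed device ratios, site split, variances and correlation, none of which the protocol gives. If the devices are in fact cross-calibrated, the scale problem disappears and only the missing site term remains.

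The T2 entrants add a further, unquantified reason for a site term. The article does not say how a patient without T0 enters a model adjusted for T0. If T2 serves as their baseline, the offset is absorbed as for everyone else.

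**What to change.** - Include site as a fixed effect in the model for leg-extension and chest-press strength.
- State that each patient is tested on the same device throughout, and report any cross-calibration that exists.
- Prespecify a scale-free contrast for these two tests: either log strength with log baseline, reported as a BFR-T/control ratio, or change standardized within site.
- Say in the outcome description that equipment is site-specific.
- Leave handgrip, for which one device is named, in its own unit.

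This changes wording only and needs no new data. The cost is that results appear as percentages or SD units. The log ratio removes only multiplicative device differences. Within-site standardization also removes offsets, but depends on SDs estimated from few patients per site.

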
### Plans to promote participant retention and complete follow-up {18b}

The research team has successfully completed a large randomized controlled trial and has experience regarding patient recruitment and possible dropout rates and complications that can occur when conducting clinical exercise studies. Taking these types of unexpected factors into consideration, the inclusion rate is expected to be 3 patients per month meaning that the data collection will be completed at the end of 2024.

### Data management {19}

Data is collected and entered exclusively by the study research staff. All hard copies of forms are kept in a locked filing cabinet at Karolinska Institutet. Data are entered into computer files in a re-identifiable format (participant numbers only) and password protected. Participants will not be identified in the resulting manuscripts and reports. The data monitoring committee for the current study is made up of the research project staff only and does not include representatives from the funding bodies, nor will it be influenced in any way by these funding bodies. Only the study researchers have access to the dataset.

### Confidentiality {27}

Information collected directly from participants will be in re-identifiable form and any information collected for, used in, or generated by this project will not be used for any other purpose. Only the study investigators will have access to study information.

### Plans for collection, laboratory evaluation, and storage of biological specimens for genetic or molecular analysis in this trial/future use {33}

Biological material will be collected in the form of biopsy material (muscle), plasma, and serum. The material will be stored in a project-specific research biobank at the Norwegian School of Sport Sciences. A small amount (≈100 mg) of muscle tissue will be obtained by the percutaneous needle technique under local anesthesia [21]. The muscle biopsy will be immediately snap frozen in liquid nitrogen and the samples will then be stored in – 80° until used for immunohistochemistry (5–10 μm sections will be cut and stained for relevant markers for capillaries per muscle fiber, satellite cell content, and macrophage infiltration), and protein quantification (samples will be determined for protein concentration by a protein assay, and immunoblotting will then be performed using relevant antibodies for markers of autophagy, mitophagy, and muscle catabolism) [22]. Blood samples (approximately 10 mL) will be collected and then analyzed with proteomics and metabolomics methods.

## Statistical methods

### Statistical methods for primary and secondary outcomes {20a}

Data will be analyzed using the IBM SPSS (Statistical Package for the Social Sciences) 26 statistical package for Windows (SPSS, Chicago, IL, USA). For the quantitative analysis, descriptive statistics, ANOVA, and chi-squared tests will be used to describe and compare baseline characteristics. For longitudinal analysis, linear mixed modeling adjusted for baseline values (T0) of the outcome will be used to detect any significant differences between the two groups from pre- to post-intervention as well as at follow-up 6 months following surgery. Group-by-time interaction will be included as a fixed effect. Corresponding effect sizes will also be calculated. Chi-squared tests and corresponding odds ratios will be calculated for hospitalization rates. All tests will be 2-tailed and statistical significance set at *p* ≤ 0.05.

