### Participant timeline {13}

Study outcomes will be measured at baseline (T0) and immediately (1–4 weeks) after the prehabilitation period (T1), after surgery prior to the rehabilitation period (T2), and after the 5–6-week postoperative rehabilitation period (T3). A follow-up assessment (T4) will take place 6 months following surgery. Patients with short time-to-surgery will only perform (T0) prior to surgery or will be included at (T2) for the rehabilitation period. Focus group or individual interviews will take place sometime following the exercise intervention. Hospitalization rates, prognostic- and blood markers will be assessed retrospectively at (T4) through the patients’ medical records. Baseline testing will begin immediately as participants are recruited and randomization will occur directly after the initial testing session (T0). Exercise training for the intervention group will start once participants have completed baseline testing. See Fig. 2 for an overview of the study design and measurement outcomes and time points.

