### Methods in analysis to handle protocol non-adherence and any statistical methods to handle missing data {20c}

Since the linear mixed model includes all available data (i.e., T1, T2, T3, and T4), intention-to-treat analysis is possible without imputing data.

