Due to the COVID-19 pandemic, the study start was delayed for almost 1 year. The initial plan was to include a more homogenous group: patients diagnosed with pancreatic or biliary tract cancer undergoing a pancreaticoduodenectomy; however, there were major challenges with the inclusion rate resulting in the study taking longer and risking a loss of statistical power. Amendments were made to the original plan to expand the inclusion criteria to patients undergoing either pancreaticoduodenectomy or laparoscopic surgery and to also patients with malignancies in the liver amendable for surgical resection. These changes were approved by the Swedish Ethical Review Authority and the Norwegian Regional committees for medical and health research ethics. We are aware that this will result in a heterogeneous group of patients. There is considerably less risk of complications for patients undergoing laparoscopic surgery compared to a pancreaticoduodenectomy; however, these potential differences will be adjusted for in the statistical analysis. Moreover, time to surgery and post-surgery recovery are similar across the diagnoses. In this study, we decided to include any patient who is diagnosed with resectable pancreatic, biliary tract, or liver cancer regardless of time-to-surgery which means that some patients will only have time to perform (T0) before surgery, while some will perform both (T0) and (T1). In some cases, time-to-surgery is only a few days which means that inclusion is not possible at (T0) but will instead take place at (T2). The reason for including patients at (T2) is that time-to-surgery is significantly shorter at the Norwegian site; consequently, amendments to the original plan had to be made to accommodate for the reduced time-to-surgery. We will perform a subgroup analysis to evaluate the rehabilitation effect (T2 to T3). Other amendments to the original plan include the addition of digitally supervised exercise and an exercise diary to be able to monitor exercise adherence more efficiently.

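### Patients may enter at T2, but the mixed model adjusts for the T0 value, so as written it drops these randomised patients and the intention-to-treat statement is wrong for them

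*Protocol article*

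**What the plan says.** All references are to the protocol article.

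- **Model.** Statistical methods {20a}: "linear mixed modeling adjusted for baseline values (T0) of the outcome will be used to detect any significant differences between the two groups". The section on additional analyses {20b} repeats the adjustment: "For the primary outcome the model will, besides being adjusted for the baseline value, also be adjusted for diagnosis and type of surgery".
- **Entry.** Participant timeline {13}: "Patients with short time-to-surgery will only perform (T0) prior to surgery or will be included at (T2) for the rehabilitation period". The Discussion explains that time to surgery can be only a few days, so that "inclusion is not possible at (T0) but will instead take place at (T2"), and adds: "The reason for including patients at (T2) is that time-to-surgery is significantly shorter at the Norwegian site".
- **Randomisation.** Sequence generation {16a}: "After baseline assessments, the participants are randomly allocated by the ALEA randomization software". The Participant timeline places randomisation straight after the T0 session, which cannot apply to a patient who joins at T2.
- **Missing data.** Section {20c}: "Since the linear mixed model includes all available data (i.e., T1, T2, T3, and T4), intention-to-treat analysis is possible without imputing data".
- **Provision for late entrants.** Section {20b} and the Discussion plan an additional analysis: "We will perform a subgroup analysis to evaluate the rehabilitation effect (T2 to T3").

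No section redefines baseline for T2 entrants or says what happens when the T0 covariate is absent.

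**The concern.** According to the Discussion, T2 entry was added by amendment. The model and the missing-data statement still describe a trial in which everyone has a T0 measurement. A patient first seen at T2 is randomised, and may be treated and measured at T3, but cannot enter a model that requires a T0 value.

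Three things are at stake:

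- The primary analysis would not include everyone randomised, although the plan says that it can.
- A trial of 52 patients loses power that it can hardly spare.
- The loss would probably fall mostly on the Norwegian site, because its shorter time to surgery is the stated reason for T2 entry.

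If nothing is settled beforehand, the analyst will have to drop these patients, substitute T2 or impute, and will make that choice once outcome data exist. The ultrasound assessors are not blinded.

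**Working it through.** **Step 1: who can be in the model.** The model needs a T0 value as a fixed-effect covariate and takes T1 to T4 as outcomes.

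| Patient type | T0 covariate | Later outcomes | Used by the model as written |
|---|---|---|---|
| T0 entrant with T1 | yes | yes | yes |
| T0 entrant without T1 | yes | yes | yes (a missing outcome is tolerated) |
| T2 entrant | no | yes | no (every row lacks the covariate) |

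A T0-adjusted mixed model was prepared on simulated data for 52 patients, 10 of them without T0. With complete-covariate handling it could use 42 patients. Section {20c} is therefore right for the first two rows and wrong for the third.

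**Step 2: reproduce the planned size.** Inputs from Sample size {14}: change of 1 mm, standard error of measurement 0.8 mm, 80% power, two-sided alpha 0.05, 42 evaluable patients, 25% dropout, 52 enrolled.

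- Formula: n per arm = 2 × (1.960 + 0.842)² × (SD / 1)².
- With SD = 0.8: 10.05, so 11 per arm and 22 in total. This does not match.
- With SD of change = 0.8 × √2 = 1.13 mm (two measurements, each with error 0.8): 20.09, so 21 per arm and 42 in total. This matches.

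The √2 conversion is not stated in the article. It is inferred because it reproduces the 42. The standardised effect is then 1 / 1.13 = 0.884, and t-test power at 21 per arm is 79.8%.

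**Step 3: power when T2 entrants are lost.** Completers after the planned dropout: 52 × 0.75 = 39. The share f of T2 entrants is not given, so the range is an assumption. Patients left in the model: 39 × (1 − f). Power is for a two-sample t-test with standardised effect 0.884, equal arms and two-sided alpha 0.05.

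| Share entering at T2 (assumed) | Patients in the model | Power |
|---|---|---|
| 0% | 39 | 77% |
| 10% | 35.1 | 72% |
| 20% | 31.2 | 67% |
| 30% | 27.3 | 60% |
| 40% | 23.4 | 53% |

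The first row is the reference. The step from 80% to 77% comes from 25% dropout leaving 39 rather than 42, and has nothing to do with T2 entry. What belongs to this point is the fall from 77%: about 5 percentage points at 10% T2 entry and about 23 at 40%.

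**Step 4: why T2 cannot simply fill the T0 slot.** From the intervals in the Fig. 1 caption, T0 to T3 spans 1 + 2 + 5 = 8 to 4 + 3 + 6 = 13 weeks and includes surgery. T2 to T3 spans 5 to 6 weeks and starts after surgery. The two baselines relate differently to the T3 value, so the model has to know which one a patient has.

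**The case against.** **T2 entrants are provided for, and the full analysis plan may define their baseline.** In part. The rehabilitation analysis can use them, so they are not lost to the trial. But it is an additional analysis, not the primary comparison. Section {20b} speaks only of a baseline value, which leaves some room, but section {20a} names T0 in so many words. T0 could be read as each patient's first visit. The Fig. 1 caption speaks against that, since it ties T0 to diagnosis or the end of neoadjuvant chemotherapy, and so does the Discussion, which contrasts inclusion at T0 with inclusion at T2.

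**A selective loss does not mean a biased comparison.** This stands. A reader might infer that dropping T2 entrants distorts the group difference. The documents do not support that. Entry point depends on time to surgery, which is fixed before allocation, and randomisation is stratified by site. The exclusion removes a pre-randomisation subgroup from both arms, and those who remain are still a randomised comparison.

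**The T2-to-T3 analysis is not shown to be misleading.** This also largely stands. A reader might infer that it could reverse the sign of the effect, because T2 follows prehabilitation and surgery for anyone randomised at T0. That would need arms that differ at T2 and T0-randomised patients pooled into the analysis with T2 as baseline. The article gives no such data and does not state who is included. What remains is narrower: for T0-randomised patients T2 is a post-randomisation value, so their T2-to-T3 change is not a comparison protected by randomisation.

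**The power figures rest on assumptions.** True. The share of T2 entrants is unknown and the SD is inferred. The range shows the sensitivity and does not predict the loss.

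**Conclusion.** The point holds. The model in section {20a}, the entry rule in section {13} and the intention-to-treat sentence in section {20c} cannot all be true. Under standard complete-covariate handling, every T2 entrant is lost to the primary model.

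The consequence is lower power, results that speak less for patients with short time to surgery (probably mostly at the Norwegian site), and an intention-to-treat label that does not fit. It is not a biased contrast among T0 entrants.

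Power is 77% without T2 entrants and about 72 to 53% if 10 to 40% enter at T2. This rests on an SD of change of 1.13 mm, on 39 completers with the same dropout in both entry groups, and on a simple two-sample comparison standing in for the mixed model. If T2 entrants prove few, the power loss is small, but the wording still needs correcting before analysis.

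**What to change.** 1. In sections {20a} and {20b}, define baseline as the last value before that patient's randomisation: T0, or T2 for those who enter at T2.
2. For T2 entrants, use every later visit as an outcome: T3, and T4 for outcomes measured then. The ultrasound outcomes are scheduled only to T3, so T3 is their one post-baseline visit for the primary outcome.
3. Add entry point and the baseline-by-entry-point interaction to the model.
4. Name the T3 group difference as the primary contrast. Report it by entry point as well, since the pooled figure combines prehabilitation plus rehabilitation with rehabilitation alone.
5. Rewrite the intention-to-treat sentence in section {20c} to match, and correct section {13} so that randomisation follows each patient's own baseline session.
6. Base the randomised estimate of the rehabilitation-only effect on patients randomised at T2. Report T2-to-T3 change in T0-randomised patients descriptively. T0 entrants who skip T1 do not belong in the rehabilitation-only estimate, because they may still have exercised briefly before surgery.

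A defensible alternative is to restrict the primary population to T0 entrants, drop the intention-to-treat label and accept or make up the lost power. A new randomisation stratum for entry point is not needed. It would split a trial of 52 patients close to the end of recruitment into four site-by-entry cells.

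The cost is mainly wording, plus a few degrees of freedom and a pooled effect over two intervention lengths.
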